# Magnetoencephalography study of the Xingnao Kaiqiao acupuncture during acupuncture and language task states in healthy volunteers: a single-blind, randomized, sham-controlled trial protocol

**DOI:** 10.3389/fneur.2026.1876482

**Published:** 2026-08-18

**Keywords:** acupuncture state, healthy volunteers, language task, magnetoencephalography, Xingnao Kaiqiao acupuncture

## Abstract

**Background:**

The Xingnao Kaiqiao acupuncture protocol is a well-established technique in traditional Chinese medicine, widely used for neurological rehabilitation, particularly in patients with post-stroke aphasia. However, the central neural mechanisms underlying both single-acupoint and multi-acupoint needling within this protocol remain largely unclear. This study aims to use magnetoencephalography (MEG) to compare the cerebral magnetic signals evoked by verum and sham acupuncture of the Xingnao Kaiqiao protocol in healthy adults, and to explore the central mechanisms associated with language task states.

**Methods:**

This is a single-blind, randomized, sham-controlled trial. A total of 40 healthy, right-handed volunteers aged 18–45 years will be recruited and randomly allocated in a 1:1 ratio to either the verum acupuncture (VA) group or the sham acupuncture (SA) group. The VA group will receive needling at the standard Xingnao Kaiqiao acupoints, following the protocol’s established manipulation techniques. The SA group will receive superficial needling at non-acupoints located 1 cun lateral to each corresponding verum acupoint, without any manipulation. MEG data will be acquired during resting state, acupuncture state (single-acupoint and multi-acupoint sequences), and language task state (picture naming and language repetition tasks). Structural MRI data will be collected for source localization. The primary outcome will be changes in MEG signals before and after acupuncture. The secondary outcome will be the Chinese version of the Massachusetts General Hospital Acupuncture Sensation Scale (C-MASS).

**Discussion:**

This study will use MEG to explore the central effects of Xingnao Kaiqiao acupuncture at both single-acupoint and multi-acupoint levels. It may add to current understanding of how acupuncture affects brain networks related to language processing. The findings may provide a neuroimaging basis for further research on the mechanisms of this classical acupuncture technique.

**Clinical trial registration:**

International Traditional Medicine Clinical Trial Registry (https://itmctr.ccebtcm.org.cn/) ITMCTR2026000214. This study was registered on 14th January 2026.

## Background

Post-stroke aphasia (PSA) affects approximately 21 to 40% of stroke survivors and is among the most disabling long-term consequences of stroke for communication. It can substantially reduce quality of life and adversely affect rehabilitation outcomes (1). Speech and language therapy (SLT) remains the cornerstone of treatment for PSA. Better recovery has been reported with SLT delivered at higher frequency, particularly when therapy is function-oriented and includes both receptive and expressive language training. In most studies, effective treatment intensity is around 2 to 4 h per week, with a cumulative dose of more than 20 to 50 h (2). Intensive aphasia therapy has been shown to produce clinically meaningful gains in both acute and chronic stages. For example, the Queen Square Intensive Comprehensive Aphasia Program reported a large effect size for speaking improvement, and this benefit was maintained at 12-week follow-up (3, 4). Nevertheless, many patients continue to experience substantial language impairment despite intensive conventional rehabilitation. This persistent unmet need has prompted continued interest in adjunctive treatment strategies (5).

Among the adjunctive approaches being explored for PSA, acupuncture has received increasing attention (6). Evidence from systematic reviews and meta-analyses suggests that acupuncture, when combined with language rehabilitation training, may improve both overall language performance and specific language domains (7). Sang et al. reported significant improvements in auditory comprehension, spontaneous speech, repetition, and naming, with more pronounced effects during the subacute stage (8). Among the acupuncture approaches used in stroke rehabilitation, Xingnao Kaiqiao (XNKQ) acupuncture has been studied most extensively. Developed by Academician Shi Xuemin, it is a standardized protocol designed specifically for stroke rehabilitation and has been incorporated into International Technical Operation Standards (9). In our prior work, we demonstrated its clinical relevance through a multicenter, sham-controlled randomized clinical trial published in JAMA Network Open in 2024. In that study, XNKQ acupuncture produced a between-group difference of 7.99% on the Western Aphasia Battery Aphasia Quotient (WAB-AQ) at 6 weeks. This exceeded the minimal clinically important difference of 5.05%. The benefit remained evident at 6 months, with a between-group difference of 10.34% (10).

Despite these encouraging clinical findings, the neural mechanisms through which XNKQ acupuncture may support language recovery remain incompletely understood. Available neuroimaging studies suggest that acupuncture may influence brain oscillatory activity. Reported changes include reduced delta power and increased alpha power in ipsilesional frontal regions, and these alterations appear to be associated with functional recovery (11). Functional MRI studies have shown that acupuncture may affect activity and connectivity in classical language-related regions, including Broca’s and Wernicke’s areas (12). Acupuncture has also been associated with corticospinal tract remodeling, reflected by increased fractional anisotropy (13), and with broader changes in functional brain networks (14, 15), including the default mode network (16), sensorimotor network (17, 18), and cognitive control networks (19). However, most mechanistic work to date has relied on fMRI, which reflects hemodynamic responses rather than neuronal activity itself and therefore has limited temporal resolution. Much of the existing literature has focused on motor recovery, whereas language-related mechanisms remain less well characterized (20).

Magnetoencephalography (MEG) offers several advantages for addressing this gap. It records neuronal activity directly, provides millisecond temporal resolution, and achieves spatial precision of approximately 3 to 5 mm (21). It is sensitive to oscillatory activity across the delta, theta, alpha, beta, and gamma frequency bands. These characteristics make MEG well suited to examining how acupuncture may modulate dynamic neural activity within language networks (22, 23). Previous MEG studies have shown that acupuncture can induce frequency-specific changes in functional connectivity, including point-specific effects on temporal cortex connectivity. Manual acupuncture has been shown to reduce beta-band power in the contralateral primary somatosensory cortex (24, 25). Even so, most of these studies have been conducted under resting-state conditions or simple sensory paradigms, and language task-related brain activity during acupuncture has received much less attention (26).

Recent advances in optically pumped magnetometer-based MEG (OPM-MEG) have opened up new possibilities for this field. Compared with conventional SQUID-based MEG systems, OPM-MEG operates at room temperature, can be adapted more easily to different head sizes, and is more tolerant of participant movement during scanning. It may provide improved sensitivity and spatial resolution (27, 28). The availability of domestically developed OPM-MEG systems has improved the feasibility of this line of work (29). Current evidence suggests that OPM-MEG performs comparably to, and in some settings better than, SQUID-MEG across a range of neuroimaging paradigms. In particular, triaxial OPM configurations can capture approximately twice the total signal and provide better interference rejection than conventional single-axis systems (30–32).

Against this background, the present study will use OPM-MEG to investigate both resting-state and language task-related brain activity in healthy volunteers receiving XNKQ acupuncture. This work may help address an important gap in current mechanistic research. By comparing single-point and multi-point stimulation, the study will examine the neural basis of acupoint combination, as previous findings suggest that multi-point prescriptions may induce broader neural activation and engage additional neurochemical pathways than single-point stimulation (33, 34). The relationship between *deqi* sensation and MEG signals will also be examined. Earlier fMRI studies support this line of inquiry by showing that *deqi* is associated with activation in the limbic-paralimbic-neocortical network, including the thalamus, parahippocampal gyrus, insula, and cingulate cortex (35, 36). As a first step, this study characterizes the normal spatiotemporal patterns of cerebral magnetic responses to Xingnao Kaiqiao acupuncture and language tasks in healthy volunteers. Because these responses reflect the language-related networks targeted by acupuncture, they provide a normative reference for subsequent investigations in patients with post-stroke aphasia.

## Methods/design

### Study design and setting

This is a single-blind, randomized, sham-controlled trial designed to investigate the central neural mechanisms of the Xingnao Kaiqiao acupuncture using MEG. The study protocol adheres to the Standard Protocol Items: Recommendations for Interventional Trials (SPIRIT) guidelines. The study flowchart is presented in Figures 1, 2.

**Figure 1 fig1:**
[figure not shown]
Flowchart of the trial. VA, verum acupuncture; SA, sham acupuncture; MRI, magnetic resonance imaging. **(a)** Immediate needling without retention. **(b)** Needle retention for 30 min with MEG recording during retention.

**Figure 2 fig2:**
[figure not shown]
Acupuncture sequence. 1, 4, 5, 6: Immediate needling (no retention). 2, 3, 7: needle retention for 30 min. W: washout period.

## Participants

### Recruitment

Eligible healthy volunteers will be recruited from the First Teaching Hospital of Tianjin University of Traditional Chinese Medicine. The study will be conducted from February 2026 to July 2026.

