### Inclusion criteria

Participants who meet all of the following criteria will be eligible for inclusion:

aged 18–45 years;right-handed;no metallic or magnetic implants, and able to cooperate with MEG and MRI scanning;no history of neurological, psychiatric, or severe medical conditions;no claustrophobia;no history of chronic pain or prior acupuncture treatment;native Chinese speakers;no acute upper respiratory infection, fever, severe rhinitis, cough, or other conditions that may affect scanning cooperation within 1 week prior to the experiment.

These criteria ensure a homogeneous sample of healthy adults without confounding neurological or medical conditions, while also ensuring safety and feasibility of MEG/MRI data acquisition (37, 38).

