### Exclusion criteria

Participants meeting any of the following criteria will be excluded:

pregnant women;individuals with extreme fear of acupuncture treatment;recent use of central nervous system medications;local skin infection at acupuncture sites;tattooing, eyebrow tattooing, hair dyeing, or hair perming within the past month;participation in other clinical trials within the past 3 months.

These exclusion criteria are designed to minimize confounding factors that could affect brain activity measurements and to ensure participant safety during acupuncture and neuroimaging procedures (39).

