### Blinding

A single-blind design will be employed, whereby participants will be blinded to their group allocation. In addition to participant blinding, the outcome assessors, MEG technicians, and data analysts will all be blinded to group assignment. Only the acupuncturist performing the needling will be aware of the allocation. At the end of the study, blinding success will be assessed by asking each participant to guess their group allocation (verum, sham, or “do not know”). Responses will be quantified using Bang’s Blinding Index (BI).

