#### SA group

Considering the practical constraints of the Xingnao Kaiqiao multi-acupoint protocol, in which spring-type placebo needles or skin-adhesive sham devices are not feasible and may compromise blinding, the SA control was designed based on published international acupuncture clinical trial protocols (10). The SA group will receive superficial needling at non-acupoints located 1 cun (approximately 20 mm, using the participant’s proportional measurement) lateral to each corresponding verum acupoint. The same type of needle (0.30 × 40 mm; Hwato Brand) will be used, and the procedure will be performed by the same qualified acupuncturist.

At each sham acupoint, the needle will be inserted superficially to a depth of 0.2–0.3 cun (approximately 4–6 mm), sufficient only to suspend the needle in the skin. No manual manipulation will be applied, and participants should not experience *deqi* sensation. Bilateral simultaneous needling and needle retention durations will be identical to the VA group. The single-acupoint sequence will be performed first, followed by the multi-acupoint sequence, consistent with the VA protocol.

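### Eligibility bars prior acupuncture treatment but not acupuncture or TCM training, although recruitment is at a TCM teaching hospital, which leaves the participant blind at a risk of unknown size

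*Protocol article*

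**What the plan says.** All references are to the protocol article.

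- **Recruitment:** "Eligible healthy volunteers will be recruited from the First Teaching Hospital of Tianjin University of Traditional Chinese Medicine". The section gives no recruitment channels, and does not say whether staff, students, visitors or the general public are approached. The study period is February to July 2026.
- **Inclusion criteria:** all listed conditions must be met. The one that concerns acupuncture is "no history of chronic pain or prior acupuncture treatment".
- **Exclusion criteria:** the only entry about acupuncture is "individuals with extreme fear of acupuncture treatment".
- **Blinding:** "A single-blind design will be employed, whereby participants will be blinded to their group allocation". Outcome assessors, MEG technicians and data analysts are also blinded. At the end, "blinding success will be assessed by asking each participant to guess their group allocation (verum, sham, or “do not know", and the answers are summarised with Bang's Blinding Index.
- **SA group:** the sham is "superficial needling at non-acupoints located 1 cun (approximately 20 mm, using the participant’s proportional measurement) lateral to each corresponding verum acupoint", at 0.2–0.3 cun (about 4–6 mm), with no manipulation and no intended *deqi*.
- **VA group, Table 1:** verum needling is manipulated to observable end-points, namely tearing at GV26 and three involuntary twitches at Lower HT1, LU5 and BL40.
- **Acupuncture-state recording:** before data collection, participants are told where the points are and in what order they will be needled.

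**The concern.** The sham differs from verum in site, depth and manipulation. A volunteer with no knowledge of acupuncture, in a parallel-group trial, sees only one of the two procedures and has little to compare it with. A volunteer who has studied the points and the technique does have a reference. The sham thus relies partly on participants not knowing acupuncture, and the criteria secure only that they have not been treated with it. These are different properties, and the gap matters more at a TCM university's teaching hospital than it would elsewhere.

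At stake is the meaning of the verum–sham contrast. A participant who knows the allocation may carry expectation, attention or arousal that differs by arm. C-MASS, the secondary outcome, is self-reported and directly exposed. The MEG measures that form the primary outcome are not self-reports, but expectation and attention could still influence them. Blinding of technicians, assessors and analysts does not remove an effect that arises in the participant.

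**Working it through.** **Step 1. Is a trained, never-treated person eligible?** Take a right-handed, healthy native Chinese speaker aged 18–45 who has studied acupuncture but never received it as a patient. Nothing in such training fails any inclusion condition or meets any exclusion condition. The published lists admit this person. One ambiguity remains: the text does not define whether needling received during training counts as treatment. If it does, some trained people are already barred. Those never needled are not.

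**Step 2. Could this person recognise the sham?** Set Table 1 beside the SA group section:

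| Feature | Verum | Sham |
|---|---|---|
| Site | Named acupoints. GV26 lies on the philtrum and CV23 on the anterior midline | 1 cun (about 20 mm) lateral to each |
| Depth | From 0.3–0.5 cun (GV26) to 2.0 cun (CV23) | 0.2–0.3 cun at every point |
| Manipulation | To tearing, to three twitches, to *deqi*, or for 1 min, depending on the point | None |

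A needle about 20 mm away from a midline point is a difference that someone who knows the point could notice. The documents support that recognition is possible. They do not show how often, or how early in the session, it would happen.

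**Step 3. Can the size be computed?** No. The share of trained participants, f, is not given. If trained participants are assumed always to guess correctly and the others to split evenly with no "do not know" answers, then for one arm

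BI = P(correct) − P(incorrect) = [f + (1 − f)/2] − (1 − f)/2 = f.

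The index returns whatever share was assumed, so it is no evidence of how large the problem is.

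**Step 4. Would the planned check be enough by itself?** It comes at the end of the study, so it cannot prevent unblinding. It is also imprecise at this size. The plan's figures reproduce: 40 × (1 − 0.20) = 32 with complete data, and 20 × 0.80 = 16 per group. Under the assumptions of step 3, SE = √((1 − BI²)/n). As an illustration only:

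- n = 20, BI = 0: SE = √(1/20) = 0.224, 95% interval −0.44 to 0.44.
- n = 20, BI = 0.25: SE = √(0.9375/20) = 0.217, interval −0.17 to 0.67.
- n = 16, BI = 0.25: SE = √(0.9375/16) = 0.242, interval −0.22 to 0.72.

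These lines show how wide the interval would be. They do not forecast the index. An index of 0.25 in an arm of 20 could not be told apart from chance guessing, which favours dealing with the matter at entry.

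**The case against.** The strongest reply is that the recruitment pool is unknown. Naming a hospital does not say that its students or staff will be enrolled, and a journal article commonly leaves channels and screening questions to the full protocol. This stands: the documents give no basis for saying that trained people will enter, or for telling the sponsor to advertise to the public, which may already happen. It does not remove the point, because the eligibility lists themselves are published and they admit trained people.

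A second reply is that the blind is exposed for everyone. Verum goes to tearing and twitches, sham is inert, and all participants are briefed on the point locations. This also stands. Barring trained people removes one source of unblinding and leaves the others.

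Third, blinding is measured and the other parties are blinded. This is correct, but measuring unblinding does not prevent it, and blinding others does not restore the participant's blind.

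A reader might go further and infer that the recruitment source defeats the participant blind, or that trained volunteers would identify the sham at the first needle. The documents support neither: they do not give the number of trained participants, and they contain no information on how quickly or reliably such a person would recognise the sham.

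**Conclusion.** The point holds as a gap in the eligibility criteria. People with acupuncture or TCM training who have never been treated are eligible, recruitment is at a TCM teaching hospital, and the sham has features that such people could recognise. This leaves the participant blind open to an avoidable risk. Its size is not given and cannot be derived: it is nil if no trained person enrols and grows with the trained share. The conclusion rests on two readings, that the published lists are the operative ones and that treatment does not include every needling received in training. It is a worthwhile, inexpensive improvement. It does not show that the trial's blinding has failed, and it changes no sample-size figure.

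**What to change.** Extend the inclusion criterion to read: *no prior acupuncture treatment, and no education, training or employment in acupuncture or traditional Chinese medicine*. Ask about this at screening.

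The stated study period ends in July 2026, so enrolment may be under way or complete. In that case, record each participant's training status and report the verum–sham comparison and Bang's index with and without trained participants, labelled as a sensitivity analysis. Training that predates randomisation is a baseline characteristic, so leaving out trained participants from both arms still compares randomised people, though in a smaller and less precise set.

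The cost is one criterion and one screening question, a smaller recruitment pool and possibly slower enrolment.

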### Inclusion criteria

Participants who meet all of the following criteria will be eligible for inclusion:

aged 18–45 years;right-handed;no metallic or magnetic implants, and able to cooperate with MEG and MRI scanning;no history of neurological, psychiatric, or severe medical conditions;no claustrophobia;no history of chronic pain or prior acupuncture treatment;native Chinese speakers;no acute upper respiratory infection, fever, severe rhinitis, cough, or other conditions that may affect scanning cooperation within 1 week prior to the experiment.

These criteria ensure a homogeneous sample of healthy adults without confounding neurological or medical conditions, while also ensuring safety and feasibility of MEG/MRI data acquisition (37, 38).

### Exclusion criteria

Participants meeting any of the following criteria will be excluded:

pregnant women;individuals with extreme fear of acupuncture treatment;recent use of central nervous system medications;local skin infection at acupuncture sites;tattooing, eyebrow tattooing, hair dyeing, or hair perming within the past month;participation in other clinical trials within the past 3 months.

These exclusion criteria are designed to minimize confounding factors that could affect brain activity measurements and to ensure participant safety during acupuncture and neuroimaging procedures (39).

### Withdrawal criteria

Participants may withdraw from the study under the following circumstances:

### Participant-initiated withdrawal

Voluntary withdrawal at any time without providing a reason and without penalty.Withdrawal due to intolerable discomfort or adverse events related to acupuncture or MEG/MRI procedures.Non-compliance with study procedures (completion rate <80%).

### Investigator-initiated withdrawal

Development of serious adverse events that, in the investigator’s judgment, make continued participation inadvisable.Discovery of previously unrecognized exclusion criteria (e.g., pregnancy, neurological condition).Protocol violations that significantly affect data quality or participant safety.Inability to complete MEG/MRI scans due to technical issues or participant factors (e.g., excessive head movement, claustrophobia).

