### Sample size calculation

Currently, there is no unified standard for sample size calculation in MEG acupuncture research (37, 40). We will therefore enroll 40 healthy volunteers (20 per group). This sample size was informed by prior neuroimaging studies (41), in which 12–24 participants per group were used to examine brain activation differences between verum and sham acupuncture. Accounting for an anticipated 20% dropout rate, complete data are expected from at least 32 participants (16 per group).

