### Randomization

Participants will be randomly assigned to the verum acupuncture (VA) group or the sham acupuncture (SA) group in a 1:1 ratio. The random allocation sequence will be generated using block randomization, stratified by sex, to ensure a balanced distribution of male and female participants across both groups. Allocation concealment will be maintained by having the research coordinator obtain the participant’s intervention assignment from sequentially numbered, opaque, sealed envelopes immediately before the first intervention session, and communicate this information exclusively to the acupuncturist.

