### Interventions

#### VA group

The VA group will receive acupuncture at the standard acupoints of the Xingnao Kaiqiao protocol. The acupoints include Neiguan (PC6, bilateral), Shuigou (GV26), Sanyinjiao (SP6, bilateral), XiaJiquan (Lower HT1, bilateral), Chize (LU5, bilateral), Weizhong (BL40, bilateral), Lianquan (CV23), and PangLianquan (Beside CV23, bilateral). Acupoint localization will follow the WHO Standard Acupuncture Point Locations in the Western Pacific Region (2020 edition). Disposable silver acupuncture needles (0.30 × 40 mm; Hwato Brand, Suzhou Medical Appliance Factory Co., Ltd., China) will be used. All acupuncture procedures will be performed by a licensed acupuncturist with at least 5 years of clinical experience.

The acupuncture procedure will follow the standardized Xingnao Kaiqiao acupuncture protocol (42), with the CV23 and Beside CV23 techniques based on the research group’s prior study published in a JAMA Network Open randomized clinical trial (10). Participants will be positioned supine. The single-acupoint sequence will be performed first, followed by the multi-acupoint sequence. The acupuncturist will needle the points in the following order: Neiguan (PC6), Shuigou (GV26), Sanyinjiao (SP6), XiaJiquan (Lower HT1), Chize (LU5), Weizhong (BL40), Lianquan (CV23), and Beside CV23. The locations and needling techniques for each acupoint are described in Table 1 and Figure 3.

**Table 1 tab1:** Acupoint locations, needling techniques, and needle retention times in the VA group.

Acupoint name	Location	Needling technique	Retention
Neiguan (PC6, bilateral)	On the anterior forearm, 2 cun proximal to the palmar wrist crease, between the palmaris longus and flexor carpi radialis tendons	Perpendicular insertion 0.5–1.0 cun; twirling-rotating combined with lifting-thrusting reducing method; bilateral simultaneous manipulation for 1 min	No retention
Shuigou (GV26)	On the face, at the junction of the upper one-third and middle one-third of the philtrum	Oblique insertion 0.3–0.5 cun toward the nasal septum; sparrow-pecking reducing method until the eyes become moist or tearing occurs	30 min
Sanyinjiao (SP6, bilateral)	On the medial lower leg, 3 cun above the medial malleolus, posterior to the medial tibial border	Perpendicular insertion 1.0–1.5 cun; twirling-rotating reinforcing method; bilateral simultaneous manipulation for 1 min	30 min

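### Scan-completion failures after randomisation can withdraw the whole participant, and because verum needling is much stronger than sham, such losses can depend on arm and bias the comparison

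*Protocol article*

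**What the plan says.** Under Withdrawal criteria, the investigator-initiated list contains "Inability to complete MEG/MRI scans due to technical issues or participant factors (e.g., excessive head movement, claustrophobia". The participant-initiated list contains "Non-compliance with study procedures (completion rate <80" per cent), although a completion threshold is a rule that the study team applies to the participant. Neither ground is limited to the time before allocation.

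Under Randomization, the envelope is opened "immediately before the first intervention session". Under Assessment timepoints, baseline language-task and resting MEG come before the first needling. Seven single-acupoint acquisitions follow, and the multi-acupoint acquisition comes last. GV26, SP6, CV23 with Beside CV23, and the multi-acupoint condition are recorded while the needles are retained. PC6, Lower HT1, LU5 and BL40 are recorded just after needling.

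The arms differ sharply in stimulation. Table 1 specifies for verum GV26 a "sparrow-pecking reducing method until the eyes become moist or tearing occurs", and for Lower HT1, LU5 and BL40 manipulation until three involuntary twitches. Under SA group, sham needles go in 4–6 mm, are not manipulated and are not meant to produce deqi.

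Under Sample size calculation, "complete data are expected from at least 32 participants (16 per group"), after an anticipated 20% dropout from 40.

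**The concern.** Head movement, failure to finish a scan and low completion are data-quality events that occur after randomisation and may be consequences of the assigned needling. If such an event ends a person's participation, the people who remain in the verum arm may no longer be comparable with those who remain in the sham arm.

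The order of the session adds to this. The multi-acupoint recording and the final resting recording come last, so any withdrawal during the single-acupoint sequence loses both. No later choice of analysis set can recover recordings that were never made.

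The between-group t-tests on MEG change, and the use of C-MASS scores from the same people, are what is at stake. An even 16/16 split does not protect them, because equal numbers lost for different reasons still leave different kinds of people in each arm.

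**Working it through.** **1. The plan's own figure.** 40 × (1 − 0.20) = 32, or 16 per group. This reproduces. With independent 20% dropout, the chance of at least 32 completers is 59% and of at least 16 in both arms 0.63 × 0.63 ≈ 40%. The stated minimum is therefore an expectation and not a floor. The same 8 losses could fall as 16/16, 14/18 or 12/20 completers (verum/sham).

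**2. Is the harm lost power?** Assume two-sided alpha 0.05 and 80% power (neither is in the article). The detectable difference is (1.960 + 0.842) × √(1/n₁ + 1/n₂): 0.99 SD at 16/16 and 1.02 SD at 12/20. Power hardly changes, so the issue is bias.

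**3. Mean shift if removal is related to response.** Let ρ be the correlation between the tendency to be removed and the MEG response, with response normal. Removing the top fraction q of the verum arm shifts its mean by −ρ × φ(z)/(1 − q), where z is the standard normal quantile at 1 − q.
- q = 0.20 (4 of 20): φ(0.8416)/0.80 = 0.350, so the shift is −0.105 SD at ρ = 0.3 and −0.175 SD at ρ = 0.5.
- q = 0.40 (8 of 20): φ(0.2533)/0.60 = 0.644, so the shift is −0.193 and −0.322 SD.

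**4. Effect on the planned t-test.** Simulation of 10,000 trials per row: 20 per arm, true difference zero, losses related to response in verum and random in sham.

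| Losses VA/SA | Analysed | Bias, ρ = 0.3 | Bias, ρ = 0.5 | Type I error, ρ = 0.3 | Type I error, ρ = 0.5 |
|---|---|---|---|---|---|
| 4/4 | 16/16 | −0.10 SD | −0.16 SD | 6.1% | 7.4% |
| 6/2 | 14/18 | −0.15 SD | −0.24 SD | 7.5% | 10.5% |
| 8/0 | 12/20 | −0.19 SD | −0.31 SD | 7.9% | 13.8% |

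At ρ = 0 the bias is zero within simulation error and type I error is about 5% for every split. The simulated shifts are slightly smaller than in step 3 because each arm has only 20 people. The minus sign means only that larger responses are lost. For a metric that falls with needling, the sign reverses.

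**5. The 80% threshold.** No denominator is given, and it matters. Over the eight needling acquisitions (7 single + 1 multi), missing two leaves 6/8 = 75%, below the threshold. Over all MEG items described under Assessment timepoints and Language tasks, the count is 2 tasks + 1 baseline rest + 7 single + 3 rests after needle removal + 1 rest before multi + 1 multi + 1 final rest = 16. Missing two non-retained acquisitions then leaves 14/16 = 87.5%, above it.

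**6. Is incompletion plausible?** Six intervals between single acupoints plus one before the multi-acupoint sequence make seven. At the washout times under study (0.5 to 2 h), they total 3.5 to 14 h, before any recording or retention time. The text does not say how this is spread over visits.

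**The case against.** Several objections have force.

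- **Discarding of data.** A reader might infer that a withdrawn participant's existing recordings are thrown away. The article does not say so. The completer count under Sample size calculation is a forecast and not an analysis rule, and analysis sets may be defined in a document not shown. What stands is the loss of later recordings and of the person from continued participation.
- **Tearing and twitching.** A reader might take these as marks of strong reactors who then move and are removed. They are manipulation endpoints sought in every verum participant. At Lower HT1, LU5 and BL40 the recording follows needling, so twitches need not fall inside it, and tearing is not head movement. The remaining routes are the recordings during retention, general discomfort and incompletion.
- **Existing safeguards.** MEG data preprocessing already rejects bad channels, muscle-contaminated segments and artefact epochs, and the article describes the system as tolerant of movement. This should reduce the number of events, but it does not cancel the person-level rule. Blinded technicians and analysts do not cure the problem either, since the cause of loss can differ by arm without anyone knowing the allocation.
- **Scan tolerance.** Listing "no claustrophobia" at entry and claustrophobia again as a withdrawal ground is not a contradiction, because it may first appear in the scanner. Baseline MEG already precedes needling. Only the timing of the structural MRI is unstated in the text.
- **Another route.** "Withdrawal due to intolerable discomfort or adverse events related to acupuncture or MEG/MRI procedures" is perhaps the likeliest arm-related loss. That is true, but it belongs to the participant and to safety, and should not be restricted. It can be reported by arm.

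**Conclusion.** The point holds in limited form. The withdrawal rules allow events after allocation that concern data quality to remove a whole participant, under stimulation that differs strongly by arm. That can bias the verum–sham comparison even when losses are balanced. The documents do not show that it will.

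The size rests on an assumed correlation and an assumed split of the 8 planned losses. It runs from zero at ρ = 0, through about −0.10 to −0.16 SD for an even split at ρ = 0.3 to 0.5, to −0.31 SD if all losses are verum and ρ = 0.5. Larger values of −0.35 SD (4 verum losses) or −0.64 SD (8) follow only if removal tracks response perfectly, which nothing in the article supports. It also cannot be said that missing two needling acquisitions triggers withdrawal, since the denominator is undefined.

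This is a rule worth changing because the change is cheap. It is not evidence that the randomised comparison is already broken.

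**What to change.** 1. After allocation, let head movement, technical failure or completion below 80% exclude only the affected acquisition and not the participant. This extends to the acquisition what the preprocessing section already does for channels, segments and epochs.
2. Keep all usable recordings of every randomised participant in the assigned arm, including those made before any withdrawal.
3. Report lost acquisitions and withdrawals by arm and reason.
4. If the 80% figure is kept as a compliance descriptor, define its denominator and move it out of the participant-initiated list.
5. Confirm that the structural MRI, like the baseline MEG, is completed before the envelope is opened, so that people who cannot be scanned are found before allocation.

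Withdrawals for consent or safety stay unchanged, and nothing in the needling alters. The cost is protocol wording and confirmation of the order of procedures already planned. The downside is that some participants will contribute only part of the recordings, so the number analysed will differ between acquisitions.
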